### Randomization and blinding

Following the informed consent and baseline evaluations, participants at each center will be locally randomized to the tDCS, tACS and placebo groups in a 2:2:1 allocation ratio, giving more weight to the active interventions. A staff member who is not involved in any study procedures will be responsible for creating the randomization list, generated by an automatic web-based randomization program from GraphPad Prism, and monitoring it during the study. The number of participants in the sham group was planned as half of those receiving tDCS or tACS. This 20% sham allocation was decided upon on account of it being the smallest and statistically correct number of patients that can stay without treatment. Given prior studies in populations with chronic pain, which showed clinically relevant remission of symptoms after tES treatments, we expect a positive effect of the technique in our trial [11]. The corresponding 20% of the sample is sufficient to achieve an analysis with sufficient statistical power. Therefore, for ethical reasons, we are keeping the size of the untreated group to a necessary minimum given our sample size.

The study will be triple-blinded, as the patient and caregiver, the study clinician and/or interventionist, and the evaluator will be blinded to the group assignment until the completion of the trial. The NeuroConn Data analysis will also be conducted in a blinded manner. The device used for the tES intervention (DC-STIMULATOR MOBILE, neuroConn GmbH, Ilmenau, Germany) allows complete blindness. Only the research members in charge of generating the randomization list will have access to the patient’s intervention status. The success of blinding will be measured at the end of the intervention by asking the patients what type of stimulation they think they received.

Unblinding will take place once recruitment and subsequent data analysis are completed. However, the coding system includes a mechanism that allows rapid identification of the treatment procedure in a medical emergency such as (1) in case of administration of an incorrect stimulation dose that could endanger the patient; (2) cases in which further treatment of the patient depends on knowledge of the treatment provided by the medical device;, and (3) in case of serious adverse events.

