### Sample size calculation

To calculate the sample size, we considered the data of a recent meta-analysis of 13 studies with data originating from 398 participants with chronic pain. Active tDCS has been reported to have a superior effect than sham with a medium-large size effect (standardized mean difference= −0.76 +/– CI 95% = −1.24) [100]. However, the effect size of tDCS varied considerably between studies, for which reason we decided to achieve small effect sizes to ensure the robustness of our results. Thus, we used G*Power software (Version 3.1.9.7) to calculate the sample size sufficient to reach a small effect size (f = 0.095) with mixed model analysis of variances (ANOVA), setting alpha at 0.05 and power (1-β) at 0.9. The sample was estimated as 291 participants. Thus, we will recruit 450 participants to compensate for eventual dropouts or attrition during the treatment or at the follow-ups (approximately 30%).

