### Statistical analysis plan

The statistical plan was accepted by the ethical committees of the involved centers. To ensure that the treatment groups (tDCS, tACS, sham) were comparable, we will perform a one-way analysis of variance (ANOVA) for age, gender, clinical outcomes and a chi-squared analysis for the demographic variables, medication pattern, and the rest of categorical variables.

 Aim 1 and 2: We will implement an intention-to-treat analysis approach, including all randomized participants who received at least 10 consecutive stimulations [101, 102]. Missing data will be imputed following the method that allowed us to obtain the best adjustment. We will address our primary and secondary hypotheses using two complementary statistical approaches (Classical Frequentist and Bayesian statistics) to enhance the robustness of our findings (similar to Samartin-Veiga et al., 2022), as well as time series analysis. We will calculate mixed model ANOVAs for each outcome (scores of self-report questionnaires for both patients and care providers, as detailed in Sect. 4.2; QST and EEG measures) with the intervention group (tDCS, tACS, sham) as a between-subject factor and time (T0, T1, T2, T3) as a within-subject factor. Age, sex, and cancer characteristics (i.e., type extension, evolution, previous treatments) will be included as covariate variables in the statistical analysis. In the presence of statistically significant main effects and group*time interaction effects, Bonferroni-Holm corrected post hoc analyses will be conducted for multiple comparisons. The effect size will be computed as eta squared η2 and interpreted based on Cohen’s benchmark categorization (small, η2 = 0.01; medium, η2 = 0.06 and large, η2 = 0.14) [103]. The normality of residuals will be tested using Shapiro Wilk’s test and normality plots. The homoscedasticity assumption for mixed model ANOVA will be tested with the Levene’s test and the sphericity will be tested using the Mauchly’s test for repeated factors. In case of sphericity deviation, Greenhouse-Geisser corrections will be used.

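### The effect size is fixed as eta squared with Cohen's cuts, a number whose label depends on the design and the ANOVA term and does not track the benefit of either stimulation over sham

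*Protocol article*

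**What the plan says.** The section Statistical analysis plan of the protocol article sets out mixed ANOVAs for each outcome. Group (tDCS, tACS, sham) is the between-subject factor and time (T0, T1, T2, T3) the within-subject factor. Significant main effects and interactions are followed by Holm-corrected post hoc comparisons. It then states: "The effect size will be computed as eta squared η2 and interpreted based on" Cohen's categories, given as "small, η2 = 0.01; medium, η2 = 0.06 and large, η2 = 0.14". No other effect measure is named for these models. The text does not say whether eta squared is classical or partial, or to which term it applies.

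Three other statements bear on this:

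- Randomization and blinding: patients are "locally randomized to the tDCS, tACS and placebo groups in a 2:2:1 allocation ratio".
- Sample size calculation, on the cited meta-analysis (SMD −0.76): "Active tDCS has been reported to have a superior effect than sham with a medium-large size effect". The planning value is on another scale: "calculate the sample size sufficient to reach a small effect size (f = 0.095").
- Specific aims and hypotheses: Aim 1 compares tDCS and tACS with sham, and expects the two to differ in their effect on pain intensity.

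**The concern.** Aim 1 asks signed, pairwise questions: does tDCS lower pain against sham, does tACS, and by how much? Eta squared is a share of variance. It cannot show direction, and for any omnibus term it merges the two active arms. Its size also depends on features unrelated to benefit: the sham share, the number of visits averaged, the term chosen, and the within-patient correlation if the partial form is used. Fixed cuts on such a number give a label that can change while the benefit stays the same. At stake is how the result will be described: a worthwhile difference could be called *small*, or one difference could carry two labels depending on which line of the output is read.

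**Working it through.** **The plan's own figure.** The stated settings are f = 0.095 and "setting alpha at 0.05 and power (1-β) at 0.9", with the result "The sample was estimated as 291 participants". For a within-between interaction with k groups, m measurements and correlation ρ, the noncentrality is λ = f²·N·m/(1−ρ), with (k−1)(m−1) and (N−k)(m−1) degrees of freedom. With k = 3, m = 3 and ρ = 0.5 (the article gives neither m nor ρ), N = 288, and power at 291 is 0.905. So 291 is reproduced closely under those assumptions. On the ANOVA scale, f = 0.095 is η² = 0.009025/1.009025 = 0.009, next to the *small* cut of 0.01. The planning label and the analysis label therefore agree.

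**Inputs for the check.**

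- From the article: weights 0.4/0.4/0.2, four visits, d = 0.76, cuts 0.01/0.06/0.14.
- Assumed: SD of 1 at every visit, no difference at T0, no common time trend, ρ from 0.3 to 0.8, and a tACS effect equal to, half of, or none of the tDCS effect.
- Effect profiles over T0–T3: T1 only (0,1,0,0), T1–T2 (0,1,1,0), sustained (0,1,1,1), fading (0,1,0.5,0.25).

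**Formulas.** Let B be the between-arm variance at full effect, p̄ the mean of the profile, V its variance, and μ the weighted mean effect.

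- B = 0.16d² = 0.0924 (tACS equal), 0.14d² = 0.0809 (half), 0.24d² = 0.1386 (null). μ = 0.8d, 0.6d, 0.4d.
- V = 3/16 (T1 only and sustained), 1/4 (T1–T2), 0.1367 (fading).
- Interaction I = B·V. Group main effect G = B·p̄². Time T = μ²·V. Total = 1 + I + G + T.
- Classical η² = I/total or G/total. Partial η² for the interaction = I/(I + ¾(1−ρ)).

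**Classical, group by time.**

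- T1 only, arms equal: 0.0173/1.092 = 0.016.
- Sustained, arms equal: 0.0173/1.139 = 0.015.
- Lowest of the twelve combinations (fading, tACS half): 0.0111/1.055 = 0.0105.
- Highest (T1–T2, tACS null): 0.0347/1.092 = 0.032.

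All are *small*. With a sustained effect, this term reaches 0.06 only at d of about 1.96 (both arms work) or 1.36 (tDCS only). These values do not depend on ρ.

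**Classical, group main effect.** Lowest (T1 only, tACS half): 0.0051/1.059 = 0.005, below the lowest cut. Sustained, arms equal: 0.0520/1.139 = 0.046, *small*. Highest (sustained, tACS null): 0.0780/1.121 = 0.070, *medium*.

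**Partial, group by time.** Sustained with equal arms gives 0.032 at ρ = 0.3, 0.044 at 0.5, 0.072 at 0.7 and 0.104 at 0.8. It crosses 0.06 where 0.0173/0.06 − 0.0173 = 0.271 = ¾(1−ρ), so at ρ of about 0.64. Over all combinations it runs from 0.0111/(0.0111 + 0.525) = 0.021 to 0.0347/(0.0347 + 0.15) = 0.188.

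**Single visit, arms equal.** Three arms at 2:2:1: 0.0924/1.0924 = 0.085. tDCS against sham at 2:1: (2/9)d² = 0.1284, and 0.1284/1.1284 = 0.114. Both are *medium*.

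**Allocation alone.** For three arms at one visit, changing 2:2:1 to 1:1:1 replaces 0.16 by 2/9 and moves η² from 0.085 to 0.114 with no change in benefit.

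**In pain points.** 0.76 SD is 1.1 to 1.9 NRS points for an assumed SD of 1.5 to 2.5. The article gives no SD.

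**The case against.** The strongest reply is that the change of label comes from changing metric. The 0.76 is a pairwise SMD, and its nearest counterpart here is tDCS against sham at one visit. That gives 0.114, *medium* and towards the *large* cut, which fits the sample size section's description. The effect-size sentence follows the one on post hoc comparisons and is not tied to the interaction. This stands. A reader might infer that the plan will call its own medium-large effect *small*, but the documents do not support that as a fact. It holds for the classical interaction term, not for every term or form the sentence allows.

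A reader might also infer that no result in pain points will be given. The article does not say so. It is a condensed account, and a fuller plan may contain mean differences and confidence intervals. The point rests on the measure and labels that the article fixes, not on an omission.

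Third, the article plans post hoc comparisons and Bayesian analyses, and has a clinical yardstick in the responder definition (at least 30% reduction from T0 to T1). This is partial relief: the responder rule is used to profile patients, and the article states no comparison of responder rates between arms.

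Finally, the ANOVA sentence points in parentheses to the section on secondary outcomes. It also says it covers each outcome and follows a statement about primary and secondary hypotheses, so reading it as including pain intensity is fair.

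**Conclusion.** The point holds as a badly chosen effect measure with a labelling rule fixed in advance. One benefit, d = 0.76 for tDCS, falls below *small*, at *small* or at *medium* depending on the term, on the form, on how long the effect lasts and on what tACS does: 0.0105 to 0.032 for the classical interaction, 0.005 to 0.07 for the classical group main effect, 0.02 to 0.19 for the partial interaction, and 0.085 or 0.114 at one visit. The figures rest on equal SDs, no T0 difference, the four profiles and three tACS scenarios listed, and ρ between 0.3 and 0.8. None of these assumptions comes from the article. That the number is unsigned and depends on allocation needs none of them. No test is invalid because of this, and neither the 291 nor the recruitment target is called into question. It is an inexpensive improvement to how the result will be sized and described.

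**What to change.** In the Statistical analysis plan, replace the effect-size sentence. For pain intensity, make the effect measure the adjusted mean difference in NRS points for tDCS minus sham and, separately, for tACS minus sham, at a named time point and with a 95% confidence interval. An SMD may be added for comparison with the literature. If eta squared is kept, present it as a supplement, state whether it is classical or partial and for which term, and drop Cohen's labels.

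The change is one sentence. It needs no new data and costs no power. The only loss is slightly less uniform reporting across the many outcomes.

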**Methods:**

This article describes the protocol of a multicenter, sham-controlled, parallel-arm, triple-blinded randomized clinical trial assessing home-based tDCS and tACS in the treatment of cancer patients with persistent pain. 450 patients between 18 and 75 years old will be enrolled in this study. Treatment consists of 15 consecutive daily sessions of either anodal tDCS at 2 mA targeting the primary motor cortex or 10 Hz tACS targeting the dorsolateral prefrontal cortex. Following randomization (2:2:1 ratio), 180 patients will receive active tDCS, 180 patients active tACS, and 90 patients sham stimulation. The primary outcome is self-reported pain intensity on a numerical rating scale (NRS) assessed daily (15 days pre-treatment, 15 days during treatment and 15 days post-treatment). The secondary endpoints are medication intake, other cancer-associated symptoms and quality of life. We will also analyze psychophysical and neurophysiological correlates of ascending and descending pain processing using QST and EEG paradigms. Besides the NRS, which will be reported daily, assessments will be conducted at baseline (T0) and at three time points post-intervention (T1, T2, and T3).

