### Specific aims and hypotheses

This multicenter study will address many aspects of cancer-related persistent pain including its potential treatment with repeated tES and assessment of the effectiveness of the therapy using self-reported assessment of different symptoms of the disease, psychophysical testing using QST and neurophysiological testing using EEG. The aims and hypotheses of the study are as follows:Aim 1: To determine the therapeutic effects of 15-day home-based anodal tDCS and tACS interventions (compared to sham stimulation) on pain intensity (primary outcome), other dimensions of pain (pain unpleasantness, catastrophizing, interference), quality of life, cancer-associated symptoms (fatigue, depression, anxiety, sleep fragmentation, cognitive impairment), and global functioning among patients with cancer-related persistent pain. We hypothesize that compared to sham, tDCS and tACS will reduce clinical pain and associated symptoms as well as improve quality of life and global functioning. We expect that anodal tDCS might have a stronger effect on pain intensity, while tACS can have a stronger effect of decreasing stress, emotional processing of pain and improving quality of life. We will also test the feasibility of the home-administered tES (analyzing dropout rates, satisfaction scores, adverse and side-effects…). The potential long-term benefits of the interventions will also be addressed at three and six months post-treatment follow-ups.Aim 2: To identify psychophysical and neurophysiological predictors and mediators of tES-induced analgesia in patients with cancer pain. We hypothesize that the improvement in clinical pain will be mediated by intervention-induced adaptive changes in (i) nociceptive and pain modulatory system using QST indices and through contact heat-evoked potentials (CHEPs) using concurrent heat painful stimuli and EEG, as well as (ii) in oscillatory activity measured by resting state EEG.Aim 3: To identify responders to the tES interventions based on clinically relevant reduction in pain intensity (≥ 30%) and to characterize them according to central pain biomarkers using QST, EEG measures and/or sociodemographic, climical and disease related data. We hypothesize that indices of pain modulation and perception will be sensitive to predict treatment outcomes.

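### Equal variance across arms of 180, 180 and 90 is only checked with Levene's test; if the arms' variances differ, pooled standard errors could be off by roughly 3% to 10%

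*Protocol article*

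**What the plan says.** The Methods part of the abstract fixes the arms: "Following randomization (2:2:1 ratio), 180 patients will receive active tDCS, 180 patients active tACS, and 90 patients sham stimulation". Under Randomization and blinding the same imbalance is deliberate: "The number of participants in the sham group was planned as half of those receiving tDCS or tACS".

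The section Statistical analysis plan specifies a mixed ANOVA for each outcome, with group (three levels) between patients and time (T0 to T3) within patients. Holm-corrected post hoc comparisons follow significant effects; their error term is not stated. On assumptions, "The homoscedasticity assumption for mixed model ANOVA will be tested with the" Levene's test, and sphericity is tested with Mauchly's test. A consequence is attached only to the second check, namely the Greenhouse-Geisser correction. Nothing is said about what happens if Levene's test rejects, or what protects the analysis if it does not reject but the variances differ. No SD for pain intensity in any arm appears in the article.

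**The concern.** The between-arm tests of a standard mixed ANOVA use error terms pooled over all three arms. With 80% of patients in the active arms, the pooled variance is mostly theirs, while the standard error of an active-versus-sham contrast depends mainly on the smaller sham arm. If sham and active outcomes have different spread, the pooled figure is wrong for that contrast. Greenhouse-Geisser adjusts for the pattern of variances and correlations over visits and does not address this.

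A difference in spread is plausible. Aim 3 sets out "To identify responders to the tES interventions based on clinically relevant reduction in pain intensity", and the Discussion says efficacy may differ between nociceptive and neuropathic pain. If benefit varies between patients, scores in the active arms will tend to spread more than in sham. At stake are the width of the intervals and the p values for tDCS versus sham and tACS versus sham.

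**Working it through.** **Inputs.** Arms of 180/180/90 come from the article. With the article's approximate 30% loss they become 0.7 × 180 = 126, 126 and 0.7 × 90 = 63. The SD of 2 and the size of response are assumptions.

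**The plan's own figure.** The Sample size calculation uses f = 0.095, "setting alpha at 0.05 and power (1-β) at 0.9", and states "The sample was estimated as 291 participants". A noncentral-F calculation for the group-by-time interaction with 3 groups, 3 measurements and correlation 0.5 (the last two are assumptions) gives N = 287, or 288 in equal groups, with power 0.905 at 291. The figure is reproduced within 3%. It takes one common variance and says nothing about unequal ones.

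**Standard error ratio.** Let r = sham SD / active SD, with the active variance set to 1. The pooled variance is about 0.8 + 0.2r². For one active arm against sham at 2:2:1,

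pooled SE / true SE = √[3(0.8 + 0.2r²) / (1 + 2r²)].

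With three equal arms it is √[2(2 + r²) / (3(1 + r²))]. The approximate two-sided type I error of the pooled test is 2[1 − Φ(1.96 × ratio)].

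**Active SD under a varying response.** If half the active patients gain d points and the SD is otherwise 2, the active variance is 4 + 0.25d².
- d = 1.5 (30% of the entry score of 5): variance 4.5625, SD 2.14, r = 0.936.
- d = 3 (30% of a score of 10): variance 6.25, SD 2.5, r = 0.8.

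| Case | r | Ratio at 2:2:1 | Type I error | Ratio, equal arms |
|---|---|---|---|---|
| Equal variances | 1 | 1.000 | 5.0% | 1.000 |
| Half gain 1.5 | 0.936 | 1.031 | 4.3% | 1.011 |
| Half gain 3 | 0.8 | 1.105 | 3.0% | 1.036 |
| Sham more variable | 1.25 | 0.899 | 7.8% | 0.963 |

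Check of the third row in raw units at 126/126/63: √[5.8 × (1/126 + 1/63)] / √[6.25/126 + 4/63] = 0.3716 / 0.3363 = 1.105.

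**Simulation of the contrast at 126/126/63.** Pooled type I error was 3.2% with active SD 2.5 and sham SD 2, and 7.7% in reverse; Welch's test gave 5.1% in both. With equal variances Welch costs almost nothing (power 89.8% against 90.0%).

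**Omnibus tests.** At one time point and 180/180/90, the three-arm F test has a type I error between 3.3% and 11.7% for r from 0.5 to 2, against 4.8% to 6.1% with equal arms. The group-by-time F test (four visits, correlation 0.5, sham SD 2.5 after baseline) rejected in 7.3% of trials both without and with Greenhouse-Geisser.

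**Levene's test.** At r = 0.8 its simulated power was 38% to 47% at 126/126/63 and 57% to 66% at 180/180/90, depending on details of the simulation. It therefore misses the difference in 53% to 62% and 34% to 43% of trials.

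These checks leave out covariates, and the contrast figures refer to one time point before Holm adjustment.

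**The case against.** The strongest objection is that what follows a failed assumption check is detail an article commonly leaves to the full plan, and this article mentions a statistical plan accepted by the ethics committees that is not shown. That stands as far as mere silence goes. What survives is that the article does fix the method: a pooled-error ANOVA on 2:2:1 arms, with a pre-test as the only stated check on variance.

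Four stronger readings are tempting but not supported.

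- *The active-versus-sham intervals are wrong.* No SD is given, and with equal variances the pooled error is correct at 2:2:1. Nor does the article say that the post hoc contrasts use the pooled error; only the omnibus F test does so by construction. The responder cut-off is no evidence either: a 30% fall can be applied to any distribution, sham included.
- *Power falls materially.* Combining an active SD of 2.5 with a 1-point difference gives 84% with Welch and 79% pooled. But that SD arises when half the active patients gain 3 points, which implies a mean difference of 0.5 × 3 = 1.5 points; power is then about 99% either way. With a 1.5-point gain in half (mean difference 0.75), it is 65.2% against 63.3%.
- *False positives are inflated.* This needs sham to be the more variable arm, for which the document offers no reason. If stimulation does nothing, randomised arms share one distribution and the pooled test keeps its level.
- *The 2:2:1 allocation causes the problem.* For the pairwise contrasts it only amplifies it: for r from 0.5 to 2 the type I error runs from 1.2% to 15.0% at 180/180/90 and from 3.0% to 8.1% with equal arms.

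**Conclusion.** The point holds in conditional form, at minor to moderate size. The article relies on a variance check that has no stated consequence and that would miss a relevant difference in a third to a half of trials or more, and the correction it does name addresses another assumption. If response to stimulation varies between patients, the most plausible effect is slightly conservative inference on the active-versus-sham contrasts, provided these use the pooled error. The size rests on the assumed SD of 2, the assumed share and size of response, and a single-time-point calculation. Nothing in the document shows that the variances will differ, so this is an improvement to specify in advance rather than an error in the plan.

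**What to change.** In the section Statistical analysis plan, state that the group-by-time test and the tDCS-versus-sham and tACS-versus-sham contrasts will use arm-specific residual variances (or covariance matrices) with Satterthwaite or Kenward-Roger degrees of freedom, or Welch or sandwich standard errors, whatever Levene's test shows. Keep Levene's test as a description only. The Holm correction and the Greenhouse-Geisser sentence need no change on this account, except that the latter becomes redundant if the covariance over visits is modelled directly.

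The cost is one sentence in the plan, a small change in the analysis code and a few degrees of freedom. When variances are equal the power loss is negligible (89.8% against 90.0% in the simulation above). No change to the sample size or the allocation is needed.

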We designed the inclusion and exclusion criteria of the study to facilitate the enrolment of a representative sample of cancer patients with chronic pain, whilst optimizing the validity of our study findings and participant safety. Only participants who fulfill all the inclusion criteria and do not meet any of the exclusion criteria will be included in the study. Participants are allowed to continue their treatment-as-usual routine, including medication and non-pharmacological therapies.

Inclusion criteria:

Diagnosis of cancer affecting the lung, breast, pancreas, or colon (with/-out metastases, except for metastases in the central nervous system).Patients aged ≥ 18 years and ≤ 75 years.Cancer-related pain must be present for over 1 month prior to enrolment, with a pain intensity rated ≥ 5 on a 0–10 Numeric Rating Scale (NRS).Ability to provide informed consent.Ability to self-report pain.Life expectancy of ≥ 6 months.Ability to use the Internet and WhatsApp (Meta, California, USA, etc.) or have a person (relative or caregiver) to support them.

Exclusion criteria:

Pregnant women or women of fertile age who did not have efficacious contraception during the whole period of the study.45 kg < Body weight < 120 kg.Neurological or psychiatric diseases including epilepsy (except anxiety or depression).Unstable medical conditions (e.g., uncontrolled diabetes, uncompensated cardiac issues, heart failure, or chronic obstructive pulmonary disease).History of neurosurgery, traumatic brain injury with loss of consciousness, and/or cortical lesion. History of unexplained or repeated loss of consciousness.History of non-malignant chronic pain.Presence of implanted metallic devices in head, neck or chest, as this is a contraindication for tES.

Caregivers of patients should be consenting adults ≥ 18 years old cohabiting with the participants and able to navigate the Internet and WhatsApp.

Participants may decline to participate at any study phase, without suffering any negative consequence. They will be asked to state their reasons for dropping out for monitoring purposes.

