## Assessments and measures

### Primary outcome

The primary outcome will be self-reported cancer pain intensity, assessed by using the 11-point NRS [0: no pain due to cancer; 10: intolerable pain due to cancer] [52, 53]. The cancer pain intensity will be reported daily on the PAINLESS platform for 45 days (15 days pre-treatment, 15 days during, and 15 days post-treatment, recorded about the same time of the day). In addition, it will be reported at T0, T1, T2 and T3 visits with a recall period of 1 week. The reproducibility and cross-cultural validity of the NRS have been shown in chronic cancer-related pain, making it a reliable measure for pain assessment as a clinical outcome in many studies [54].

We will follow an intention-to-treat approach with missing data being imputed following the method that allows us to obtain the best adjustment.

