Aim 3: Patients will be classified as *responders* to the intervention if they report a mean reduction in NRS pain intensity of at least 30% at T1 compared to T0. To characterize the best responders to tES, we will also use the algorithms developed in the precursor study to profile patients using the sociodemographic and clinical variables and biomarkers studied. We will conduct tree-based methods (linear mixed-effects model trees or, in broader terms, generalized linear mixed-effects model trees), which provide a convenient way of visualizing decision rules for predicting an outcome. Personalized treatment methods will be determined by using a convenient categorical tree-based algorithm.

Statistical significance will be set at *p* < 0.05.

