The findings of small clinical trials are typically difficult to translate into clinical practice, conducive to outcomes commonly reported as statistical comparisons between the means of treatment groups. Therefore, previously validated responder analyses might provide a reliable and clinically relevant approach in analgesic studies [117, 118]. In our study, we will identify responders based on a clinically relevant pain reduction on the NRS and conduct responder analyses to profile them based on the studied biomarkers. This will aid clinicians in making decisions on whether the tES therapy is likely to work in a patient and, if so, help them to determine the expected degree of pain relief is.

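### Aim 3 counts any 30% fall in pain from T0 to T1 as response to tES and states no contrast with sham, so as written its profiles would be prognostic and not predictive of benefit

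*Protocol article*

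**What the plan says.** Aim 3, in the section on specific aims and hypotheses, is "To identify responders to the tES interventions based on clinically relevant reduction in pain intensity", with a threshold of 30%. The statistical analysis plan section makes this operational: patients are responders "to the intervention if they report a mean reduction in NRS pain intensity of at least 30% at T1 compared to T0". The best responders to tES are then to be characterised with algorithms from a precursor study, "to profile patients using the sociodemographic and clinical variables and biomarkers studied", and with linear or generalised linear mixed-effects model trees, "which provide a convenient way of visualizing decision rules for predicting an outcome". Randomised arm is not named among the inputs, and no marker-by-arm contrast is stated.

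Three other places bear on this:

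- **Participants.** Entry requires a pain rating of at least 5. "Participants are allowed to continue their treatment-as-usual routine, including medication and non-pharmacological therapies".
- **Primary outcome.** Pain intensity is rated daily for 15 days before, 15 days during and 15 days after treatment. "In addition, it will be reported at T0, T1, T2 and T3 visits with a recall period of 1 week".
- **Discussion.** On the responder profiling: "This will aid clinicians in making decisions on whether the tES therapy is likely to work in a patient".

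For Aims 1 and 2, by contrast, the same statistical section names intervention group (tDCS, tACS, sham) as a factor and refers to the group-by-time interaction.

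**The concern.** A fall in a patient's own score is not evidence that stimulation caused it. Pain ratings vary between visits, patients respond to being treated, and usual care may change between T0 and T1. The medication diary plays no part in the rule, so a patient whose analgesics were increased and whose pain then fell is labelled a responder to the intervention.

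A tree trained on that label answers a prognostic question: whose pain falls? The Discussion promises an answer to a predictive question: in whom does tES work? Only a comparison of active with sham within patient profiles can answer the second. The sham arm that makes this possible is already in the trial. Without the contrast, a marker of spontaneous improvement, or simply of a high T0 score, could be published as a biomarker of tES response.

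**Working it through.** The article gives no responder rate or sample size for Aim 3, so there is no figure of its own to reproduce. Its computed sample of 291 concerns the mixed-model ANOVA and has no bearing here.

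**1. How often is the rule met with no stimulation effect?**

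Inputs from the article: 0-10 NRS, entry rating of at least 5, 30% rule, 180 + 180 = 360 active patients and 90 sham.

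Assumed, because the article gives none: mean before selection 5-6, SD 1.8-2.2, correlation between any two readings 0.5-0.8, no treatment effect.

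Model: reading = patient level + independent error, where the patient-level variance is correlation × SD² and the error variance is (1 − correlation) × SD². Ratings are rounded and limited to 0-10. Patients enter if a screening reading is at least 5. T0 and T1 are separate later readings, and the rule is met when T1 ≤ 0.7 × T0. There were 1,000,000 simulated patients per scenario.

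| Mean | SD | Correlation | Meet the rule |
|---|---|---|---|
| 6 | 1.8 | 0.8 | 3.7% (lowest) |
| 5.5 | 2.0 | 0.8 | 5.7% |
| 5.5 | 2.0 | 0.5 | 15.5% |
| 5 | 2.2 | 0.5 | about 19% (highest) |

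Active patients labelled responders with no effect: 0.037 × 360 = 13 to 0.19 × 360 = 68. Mean T0 and mean T1 are equal to within about 0.02 points in every scenario, so these falls are variation around an unchanged average.

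**2. What does a fall unrelated to stimulation add?** With mean 5.5 and SD 2, an assumed average fall of 0.5 points, from natural course or analgesic changes, raises the rate from 5.7% to 12.2% (correlation 0.8) and from 15.5% to 23.2% (correlation 0.5).

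**3. Can a tree split on this label with no effect present?** With mean 5.5, SD 2 and correlation 0.5, the rule is met by about 12% of patients with T0 of 6 or less and about 28% of those with T0 of 8 or more. A tree could therefore select baseline pain although stimulation does nothing. At correlation 0.8 the two rates are nearly equal (about 6% each), so this depends on how variable the ratings are.

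**4. How much information does the sham arm hold?** After the planned attrition of about 30%, 0.7 × 90 = 63 sham and 0.7 × 360 = 252 active patients remain. Take an even split (31.5 sham and 126 active per node) and an illustrative 30% responder rate throughout:

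- SE of active minus sham in one node = √[0.3 × 0.7 × (1/126 + 1/31.5)] = 0.091.
- SE of the change in that difference across the split = √2 × 0.091 = 0.129.
- 95% half-width = 1.96 × 0.129 = 0.25, or 25 percentage points.

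**The case against.** The strongest reply is that a 30% rule is always a within-patient label and that comparison with sham belongs in the analysis. The article classifies patients without restricting this to the active arms. The named model trees can carry a treatment term, the precursor algorithms are not shown, and choosing a treatment per patient would fit a tree that includes allocation. Node-model detail may sit in a fuller plan. This is fair, and it means that a reader who concludes the design cannot show who benefits goes too far: the limitation holds for the analysis as written. What stands is that the published text attributes the fall to the intervention, lists only patient variables and biomarkers as inputs, names the group factor for Aims 1 and 2 but not for Aim 3, and draws a clinical conclusion that needs the contrast.

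Four further readings are tempting but not supported:

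- **That the entry threshold makes scores drift down from T0.** The threshold is an inclusion criterion reviewed at the first visit, and T0 is the separate Visit 2. By then the shift in the mean has largely passed. Null rates of 5-27%, or up to 97 active patients, arise only if T0 is itself the selecting reading, which does not fit the visits described.
- **That the label rests on two one-week-recall ratings.** The reference to a mean reduction may instead point to averaged daily ratings. The text does not settle this. Averaging would also be expected to lower the simulated rates, which model single readings.
- **That T0 to T1 spans at least 30 days.** No section dates Visit 2 against the 15-day pre-treatment diary.
- **That most active-arm responders would have responded on sham.** Shares such as 0.20/0.35 = 57% or 0.25/0.35 = 71% are ratios of chosen rates, not evidence about this trial.

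Leaving medication changes out of the label is also a common treatment-policy choice. It matters here because no sham contrast removes its effect.

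**Conclusion.** The concern holds for Aim 3 as written. The rule identifies patients who improved, and trees that predict it describe who improves, whatever the cause. They do not support the statement in the Discussion about whether tES is likely to work in a patient.

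With no effect, about 4-19% of patients (13-68 of 360 active) would meet the rule, before any placebo response or change in usual care. That range rests entirely on the assumed mean, SD and correlation, on single readings, and on screening being separate from T0. The qualitative conclusion does not depend on it, because it follows from the missing contrast.

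The randomised comparison under Aim 1 is not affected. This should be corrected before the responder analysis is run, but it does not threaten the trial's main result.

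**What to change.** In the Aim 3 paragraph of the statistical analysis plan section:

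1. Fit the model trees in all three randomised arms, with arm (active versus sham) in the node model.
2. Accept a marker as a predictor of tES response only where the active-minus-sham difference changes across the split. Describe other markers as prognostic.
3. Report responder rates as a difference from sham.
4. State that response is computed from the mean of the 15 pre-treatment daily ratings and the mean of the 15 post-treatment daily ratings, since the present wording can be read either way.

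All the data are already to be collected, so the change is to wording and analysis code only. The cost is precision. Interaction splits rest on 90 sham patients, about 63 after attrition, and a change of less than roughly 25 percentage points across an even split would be hard to tell from noise. Fewer markers will be claimed, and they should be called exploratory, with the Discussion's clinical statement softened to match.
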